### 5.3. Inclusion Criteria

The volunteer must satisfy all the following criteria to be eligible for the study:

- Healthy adult male or non-pregnant, non-lactating female, ages 18 to 50 (inclusive) at the time of screening (cohorts 1-5)
- Healthy male or non-pregnant female, ages 6-12 (inclusive) for cohort 6 and ages 13-17 –(inclusive) for cohort 7, at the time of screening.
- Have provided/had their guardians provide written informed consent/assent as appropriate, prior to screening procedures Free of clinically significant health problems, as determined by pertinent medical history and clinical examination prior to entry into the study
- Available, able, and willing to participate for all study visits and procedures
- Negative pregnancy-test for female volunteers
- Females, of childbearing potential, who are willing to use one month after vaccination effective methods of contraception.
  - A woman is considered of childbearing potential unless post-menopausal ( $\geq$  one year without menses) or surgically sterilized (tubal ligation, bilateral oophorectomy, or hysterectomy)
  - Effective contraception is defined as a contraceptive method with failure rate of less than 1% per year when used consistently and correctly and when applicable, in accordance with the product label for example:
    - Oral contraceptives, either combined or progestogen alone,
    - injectable progestogen,
    - implants of etonogestrel or levonorgestrel,
    - oestrogenic vaginal ring
    - percutaneous contraceptive patches,
    - intrauterine device or intrauterine system,
    - male partner sterilisation at least 6months prior to the female subject's entry into the study, and the relationship is monogamous,
    - male condom
- Be willing to minimize blood and body fluid exposure of others for 5 days after vaccination
  - Be advised to use an effective barrier prophylaxis, such as latex condoms, during penetrative sexual intercourse
  - Avoiding the sharing of needles, razors, or toothbrushes
  - Avoiding open-mouth kissing

### 5.4. Exclusion Criteria

The volunteer will not enter the study if any of the following apply:

- History of severe local or systemic reactions to any vaccination or a history of severe allergic reactions
- Known allergy to the components of the BPSC1001 vaccine product

- Ongoing participation in another clinical trial
- Receipt of licensed vaccines within 14 days of planned study immunization (30 days for live vaccines)
- Acute or chronic, clinically significant psychiatric, hematologic, pulmonary, cardiovascular, or hepatic or renal functional abnormality as determined by the investigator based on medical history, physical exam, ECG, and/or laboratory screening test (including sickle cell anemia)
- Viral Serologies (HBsAg, anti-HCV Ab, anti-HIV Ab)
- Any confirmed or suspected immunosuppressive or immunodeficient condition, cytotoxic therapy in the previous 5 years, and/or diabetes
- Any chronic or active neurologic disorder, including migraines, seizures, and epilepsy, excluding a single febrile seizure as a child
- Have a known history of Guillain-Barré Syndrome
- Have an active malignancy or history of metastatic or hematologic malignancy
- Suspected or known alcohol and/or illicit drug abuse within the past 5 years
- Moderate or severe illness and/or fever  $> 38^{\circ}\text{C}$  within 1 week prior to vaccination
- Pregnant or lactating female, or female who intends to become pregnant during the study period
- Administration of immunoglobulins and/or any blood products within the 120 days preceding study entry or planned administration during the study period
- History of blood donation within 60 days of enrollment or plans to donate within the study period
- Administration of chronic (defined as more than 14 days) immunosuppressants or other immune-modifying drugs within 6 months of study entry
  - For corticosteroids, this will mean prednisone, or equivalent, greater than or equal to 0.5 mg/kg/day
  - Intranasal and topical steroids are allowed
- Have an immunocompromised household member
- Any other significant finding that in the opinion of the investigator would increase the risk of the individual having an adverse outcome from participating in this study

## 5.5. Withdrawal of Volunteers

In accordance with the principles of the current revision of the Declaration of Helsinki (updated 2008) and any other applicable regulations, a volunteer has the right to withdraw from the study at any time and for any reason, and is not obliged to give his or her reasons for doing so. A parent or guardian has the right to withdraw a minor from the study at any time and for any reason, and is not obliged to give his or her reasons for doing so. Minors aged 11 and above have the right to withdraw their assent at any time and for any reason, and are not obliged to give their reasons for doing so. The investigator may withdraw the volunteer at any time in the interests of the volunteer's health and well-being. In addition the volunteer may withdraw/be withdrawn for any of the following reasons:

- Administrative decision by the investigator. This may include but is not limited to, ill health of the participant, endangerment of study staff or other participants by the behaviour of the volunteer, a possible or probable adverse event.
- Ineligibility (either arising during the study or retrospectively, having been overlooked at screening). If participants have already received a vaccination prior to becoming (or being discovered to be) ineligible, they will only be withdrawn if continued participation jeopardizes their health.
- Significant protocol deviation, which as described in ICH GCP guidelines, include those which have an impact on the safety of a participant.
- Volunteer non-compliance with study requirements
- An AE, which requires discontinuation of the study involvement or results in inability to continue to comply with study procedures

The reason for withdrawal will be recorded in the CRF. If withdrawal is due to an AE, appropriate follow-up visits or medical care will be arranged, with the agreement of the volunteer, until the AE has resolved, stabilised or a non-trial related causality has been assigned. Any volunteer who is withdrawn from the study may be replaced, if that is possible within the specified time frame. The Local Safety Monitor (LSM) may recommend withdrawal of volunteers. If a volunteer withdraws from the study, blood samples collected before their withdrawal from the trial will be used/stored unless the volunteer specifically requests otherwise.

## 5.6. Pregnancy

Should a volunteer become pregnant during the trial, she will be followed up as other volunteers and in addition will be followed until pregnancy outcome. This follow up is not only related to the health of the pregnant woman, but also includes evaluation of the new born and other pregnancy outcomes. Non-essential venepunctures will not be performed on such volunteers.

## 5.7. Potential risks for volunteers

### Phlebotomy:

The maximum volume of blood drawn over the study period (700 ml over 6 to 12 months, or 70 ml for children and adolescents, as described in table 3) should not compromise these otherwise healthy volunteers. There may be minor bruising, local tenderness or pre-syncope symptoms associated with venepuncture, which will not be documented as AEs if they occur.

### Administration of study vaccines:

Serious allergic reactions including anaphylaxis may occur and for this reason volunteers will be inoculated in a clinical area where Advanced Life Support trained physicians, equipment and drugs are immediately available for the management of any serious adverse reactions. Participants will be observed for one hour after vaccination.

### **5.8. Potential benefits for volunteers**

This trial is being conducted in a context of an EVD unprecedented outbreak, which is considered as a major and global health security concern. The vaccine recipients may benefit from protection against future EVD as Gabon has experienced also previous outbreaks. However, this trial is the first administration of VSVΔG-ZEBOV vaccine to humans. Similar trials will be performed with this vaccine coincidentally at sites in Germany and Switzerland. So the risks-benefits ratio is well known although no major or severe side effect occurred so far across the trials which are ongoing in Gabon, Kenya, Germany, Switzerland and US. There is also a rise of antibodies level in the vaccinees. Participants will be advised to not consider themselves protected against EVD at this stage of vaccine development.

## **6. Study procedures**

### **6.1. Time points**

Procedures will be performed at the time points indicated in the schedule of procedures (Table 3). Additional procedures or laboratory tests may be performed, at the discretion of the investigators if clinically necessary.

### **6.2. Screening Visit**

Screening Visit 1; Day -30 to Day -1

The Participant Information document will be provided during the recruitment phase, and before screening visits are scheduled.

Potential subjects will undergo screening no more than 30 days prior to their planned initial injection (Day 0, Visit 2). Any potential subject falling outside the 30-day window will require rescreening.

The following procedures will be performed during the screening visit:

- Briefing and review of informed consent with subject
- Written informed consent for participation in the clinical study.
- Provision of copy of signed informed consent form to subject
- Check of inclusion and exclusion criteria
- Provision of demographic information and medical history by subject (including concomitant medications)
- Physical examination
- Blood Collection: approximately 120 mL whole venous blood (10mL for children and 15mL for adolescents) for the determination of:

WBC, ALT, Creatinin, Viral Serologies (HBsAg, anti-HCV Ab, anti-HIV Ab), VSV virus isolation and replication, further analysis for humoral and cellular immune responses

Saliva and urine for VSV virus isolation

Urine pregnancy test (females only)

Potential subjects will be notified of their eligibility as soon as all lab results are available and the investigator can make an assessment. If determined to be eligible, subjects will be scheduled for their initial vaccination (Day 0, Visit 2).

Regardless of eligibility, individuals will be informed of any significantly abnormal test results, in person. Appropriate counseling will be given regarding necessary medical follow-up.

Information on individuals with evidence of reportable infectious diseases (eg. HIV and hepatitis), will be addressed to the required public health institution as applicable. Potential subjects will be notified of this possibility during their informed consent process.

Priority for blood collected from minors will be given to vaccine specific antibody tests and rVSV detection. Remaining blood will be used for cellular immune responses (if feasible).

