| Stopping rules     | 
The study will be placed on safety hold in case of occurrence of a vaccine related SAE
                                                                                                                                                                                                                                                                                                                                                                                                                                                                                                                                                                                                                                                                                                                                                                                                                                                                                                                                                                                                                                                                                                                                                        |
| Sample Size        | 
– A total of 201 volunteers will be enrolled in this trial
 
 
• 20 Volunteers aged between 18 and 50 years inclusive, who will receive <math>3 \times 10^3</math> pfu of VSV<math>\Delta</math>G-ZEBOV vaccine IM
 
• 20 Volunteers aged between 18 and 50 years inclusive, who will receive <math>3 \times 10^4</math> pfu of VSV<math>\Delta</math>G-ZEBOV vaccine IM
 
• 20 Volunteers aged between 18 and 50 years inclusive, who will receive <math>3 \times 10^5</math> pfu of VSV<math>\Delta</math>G-ZEBOV vaccine IM
 
• 39 Volunteers aged between 18 and 50 years inclusive, who will receive <math>3 \times 10^6</math> pfu of VSV<math>\Delta</math>G-ZEBOV vaccine IM
 
• 62 Volunteer aged between 18 and 50 years inclusive, who will receive <math>2 \times 10^7</math> pfu of VSV<math>\Delta</math>G-ZEBOV vaccine IM
 
• 20 Volunteers aged between 13 and 17 years inclusive, who will receive <math>2 \times 10^7</math> pfu of VSV<math>\Delta</math>G-ZEBOV vaccine IM
 
• 20 Volunteers aged between 6 and 12 years inclusive, who will receive <math>2 \times 10^7</math> pfu of VSV<math>\Delta</math>G-ZEBOV vaccine IM.
 
 |

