| Antibody isolation                                          |     |   |     |     |     |     | X   |     |     |     |  |
| Blood Volume/visit (mL) adults                              | 140 |   | 6   | 6   | 75  | 60  | 108 | 20  | 80  | 92  |  |
| Cumulative volume for study adults                          | 140 |   | 146 | 152 | 227 | 287 | 395 | 415 | 495 | 587 |  |
| Blood Volume/visit (mL) children and adolescents            | 10  |   |     | 5   | 5   | 10  | 10  | 10  | 10  | 10  |  |
| Cumulative Blood Volume/visit (mL) children and adolescents | 10  |   |     | 15  | 20  | 30  | 40  | 50  | 60  | 70  |  |

**Table 3:** Study procedures.

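### Section 6.2 sets a 15 mL adolescent screening draw, but Table 3 schedules 10 mL, and the 70 mL maximum for minors in section 5.7 rests on Table 3

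*Protocol*

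**What the plan says.** Three places in the protocol give blood volumes for minors.

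- **Section 6.2, Screening Visit.** The screening collection separates the two groups: "whole venous blood (10mL for children and 15mL for adolescents".
- **Table 3 (study procedures).** One row covers both groups, labelled "Blood Volume/visit (mL) children and adolescents". It shows 10 mL at Visit 1, nothing at Visits 2 and 3, 5 mL at each of Visits 4 and 5, and 10 mL at each of Visits 6 to 10. The running-total row, "Cumulative Blood Volume/visit (mL) children and adolescents", starts at 10 and ends at 70.
- **Section 5.7, Phlebotomy.** The risk statement gives "The maximum volume of blood drawn over the study period" as 700 mL for adults, "or 70 ml for children and adolescents, as described in table 3".

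Section 6.1 makes Table 3 the governing schedule: "Procedures will be performed at the time points indicated in the schedule of procedures (Table 3". It also leaves room for more: "Additional procedures or laboratory tests may be performed, at the discretion of the investigators if clinically necessary". The sample size section of the synopsis plans "20 Volunteers aged between 13 and 17 years inclusive".

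**The concern.** The routine screening draw of an adolescent cannot be 15 mL in one section and 10 mL in the schedule. Staff working from 6.2 and staff working from Table 3 would take different volumes from the same participant.

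The difference matters a little more than an ordinary slip because of section 5.7. That section tells ethics reviewers the most blood a minor will give and concludes that this amount is acceptable. For minors the stated maximum equals the sum of the Table 3 draws, so there is no margin to absorb a larger draw at any visit. Taken together with the later scheduled draws, the instruction in 6.2 goes over the limit on which the risk statement rests.

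What is at stake is agreement between a draw instruction and a safety maximum in a paediatric group. It is not the validity of any estimate or test.

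**Working it through.** **Inputs**

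- Table 3, minors, Visits 1 and 4 to 10: 10, 5, 5, 10, 10, 10, 10, 10 mL.
- Section 6.2, adolescent screening draw: 15 mL (children: 10 mL).
- Section 5.7, stated maximum for minors: 70 mL.
- Synopsis, planned participants aged 13 to 17: 20.

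**Step 1: reproduce the plan's own figure.** Total = sum of the per-visit draws = 10 + 5 + 5 + 10 + 10 + 10 + 10 + 10 = 70 mL. This matches the last cumulative entry in Table 3 and the figure in 5.7. Every intermediate cumulative entry also matches, so the 10 mL entry at screening is confirmed by the table itself and is not an effect of a shifted column.

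**Step 2: put the 6.2 adolescent draw in at Visit 1 and leave the rest as scheduled.** Total = 15 + 5 + 5 + 10 + 10 + 10 + 10 + 10 = 75 mL.

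| Visit | Scheduled draw after screening (mL) | Running total, Table 3 (mL) | Running total, 15 mL at screening (mL) |
|---|---|---|---|
| 1 | – | 10 | 15 |
| 4 | 5 | 15 | 20 |
| 5 | 5 | 20 | 25 |
| 6 | 10 | 30 | 35 |
| 7 | 10 | 40 | 45 |
| 8 | 10 | 50 | 55 |
| 9 | 10 | 60 | 65 |
| 10 | 10 | 70 | 75 |

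**Step 3: size of the excess.** 75 − 70 = 5 mL, and 5/70 = 7.1%. The total is 65 mL after Visit 9, so the maximum is passed only with the Visit 10 draw.

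**Step 4: sensitivity to a missed draw.** Missing one 5 mL draw gives 75 − 5 = 70 mL. Missing one 10 mL draw gives 75 − 10 = 65 mL. In either case the maximum holds.

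**Step 5: children aged 6 to 12.** Both 6.2 and Table 3 give 10 mL at screening, so the total is 70 mL and there is no mismatch.

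**Step 6: does the allowance in 6.1 explain it?** No. That clause covers extra tests that are clinically needed in an individual. The 15 mL in 6.2 is the routine volume for every adolescent screened.

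**The case against.** Several points can fairly be made on the other side.

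- **Nothing is miscalculated.** Table 3 adds up and 5.7 repeats its total. The figure of 75 mL appears nowhere in the protocol and arises only when 6.2 is combined with Table 3. This is true: the point is an inconsistency between sections, not a wrong sum. The two volumes for the same draw still cannot both be followed.
- **Section 5.7 is not an independent witness.** It takes its 70 mL from Table 3, so its agreement does not show which screening volume was intended. Section 6.2 separates the age groups on purpose, and the shared row in Table 3 could be the simplification. This stands, and it is why the fix allows for either intention. Section 6.1 does, however, make Table 3 the governing schedule.
- **Other volumes in the text also differ from Table 3.** Adult screening is about 120 mL in 6.2 and 140 mL in Table 3. Follow-up draws in 6.4 run from about 6 to 92 mL, while Table 3 has 108 mL for adults at Visit 7. These are real and worth tidying in the same edit. They do not threaten the adult maximum: the adult Table 3 total is 587 mL against 700 mL, a margin of 700 − 587 = 113 mL. For minors the margin is zero.
- **Section 5.7 describes risk and sets no rule for withholding a draw.** Correct. It is nevertheless worded as a maximum, and a stated maximum should not be exceeded by the protocol's own routine instructions.
- **The excess is trivial.** It is 5 mL, at the last visit, in at most 20 participants. This stands and fixes the severity at the lowest level.

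**Conclusion.** The inconsistency is real and wrong as written. For adolescents, 6.2 exceeds the Table 3 screening draw by 5 mL (15 against 10 mL). Followed through the schedule, it exceeds the 5.7 maximum by the same 5 mL (75 against 70 mL, 7.1%).

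The 75 mL total assumes that the 6.2 volume is drawn in full at screening, that every later draw follows Table 3, and that none is missed. Under those assumptions it applies to each participant aged 13 to 17 who completes all draws, up to the 20 planned.

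It is a minor correction. No clinical harm is claimed, and the sample size, endpoints and analysis are untouched.

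**What to change.** **Preferred:** change the adolescent screening volume in 6.2 from 15 to 10 mL, so that it agrees with Table 3 and 5.7. The cost is one figure.

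**If the sponsor intends 15 mL:** give adolescents their own per-visit and cumulative rows in Table 3, starting at 15 mL and ending at 75 mL, and state 75 mL for adolescents (70 mL for children) in 5.7. The cost is two table rows and one figure.

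Neither option changes the design, the endpoints or the analysis. While the text is open, the adult volumes in 6.2 and 6.4 can be brought into line with Table 3 as well.

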### **6.3. Study Enrollment/ vaccination (Visit 2, Day 0)**

Vaccination with BPSC1001 will occur at Visit 2. Potential participants will be listed upon information sessions and their willingness to participate. They will be then screened by block of 5-10 volunteers after informed consent signature. Eligible participants will be given a study identification number which for adults will be used for random selection to one of 5 cohorts. The randomization will be done using a software. The randomization will be detailed in a study procedure.

Subjects will have only one vaccination visit during the course of the study. Each subject will receive an injection of BPSC1001 into the outer aspect of the subject's upper arm (deltoid area). The following procedures will be performed during each injection visit:

- Review of subject's medical history (including concomitant medications) since previous visit

- Check of inclusion / exclusion criteria
- Directed physical examination (proposed injection site) and vital signs check
- Urine sample collection for determination of:  
Urine pregnancy test (females only)\*
- Injection with study product
- Post-injection observation period of at least 60 min.
- Study visits schedule , thermometer ( for axillary temperature), and ruler distribution and review of use
- Provision of emergency contact card
- Repeat examination of injection site and vital signs check
- Review of any immediate AE

\*All female subjects of childbearing potential will be required to submit a urine sample for onsite pregnancy testing on the day of injection, and the test results must be negative prior to administration of the vaccine.

#### 6.4. Follow-Up Visits: visit 3 to visit 10

There will be 8 follow-up visits (Visits 3 through 10). Table 3 outlines visits, study days, and visit windows. The following procedures will be performed during each follow-up visit:

- Review of subject's medical history (including concomitant medications and AE) since previous visit
- Directed physical examination and vital signs check
- Review solicited symptoms (4 visits; Visits 3, 4, 5, 6, )
- Collection of approximately 6 to 92 mL whole venous blood for the determination of:
  - WBC
  - Serum chemistry profiles (Creatinin, AST, ALT) will be performed only at visits 5,7,9,10.
  - Blood for immunological analyses
  - Blood for virus isolation
- Urine and saliva for virus isolation

Visit 10 (month 6) will be the final scheduled visit for all subjects. Subjects completing this visit will be considered to have completed the study. Subjects with ongoing AE at this visit will be followed until they have returned to normal, stabilized, or the event is otherwise explained or the subject is lost to follow-up.

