### 4.3. Endpoints

#### Primary Endpoints

The nature, frequency, and severity of adverse events (AEs) and/or serious adverse events (SAEs) associated with administration of BPSC1001 at 5 different doses measured as follow:

- Frequency and severity of local injection site reactogenicity signs and symptoms: pain, erythema, and induration until day 14 post vaccination (solicited local symptoms)
- Frequency and severity of systemic reactogenicity signs and symptoms until day 14 post vaccination (solicited general symptoms)
- Frequency of adverse events (AEs), severity and assessed relationship to study products until day 28 post vaccination (unsolicited AE)
- Detailed description of all serious adverse events (SAEs) until day 28 post vaccination
- Distribution of values of safety laboratory measures at baseline and at follow-up visits post-vaccination until day 28 post vaccination (reference ranges will be age appropriate)
- Number of participants with early discontinuation of vaccinations and reason for discontinuation until day 28 post vaccination

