## **Specification of Safety Endpoints**

Safety will be assessed by evaluating reactogenicity (local reactions and systemic reactions such as fever, headache, and fatigue) during specified periods of the study. The following endpoints will be evaluated:

The nature, frequency, and severity of solicited AEs occurring from the time of injection through 14 days following the procedure (memory aid to assist)

The nature, frequency, and severity of unsolicited AEs from the time of injection through 28 days following the each injection

The nature, frequency, and severity of SAEs from the time of injection through the final study visit for each subject

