### Recording Adverse Events

### Methods/Timing for Assessing, Recording, and Analyzing Safety Endpoints

Solicited AEs will be reviewed within the 14 days of vaccination utilizing the provided study memory aids. When a diagnosis is known, the AE term recorded on the CRF will be the diagnosis rather than a constellation of symptoms. The investigator will assess all AEs for seriousness, relationship to investigational product, severity, and other possible etiologies. When an event has not resolved by study closure, it will be documented on the AE CRF as “ongoing”.

The timeframe for the collection of unsolicited AEs begins at the first administration of investigational product through 28 days after the investigational product is administered. Solicited AEs will be collected from the time of administration of investigational product through 14 days following the procedure (assisted with a memory aid). The timeframe for the collection of SAEs begins at the first administration of investigational product through the end of the study.

All adverse events will be reported in concordance with ICH GCP reporting guidelines, with expedited reporting of SAEs being determined by these guidelines as well.

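### No itemised pre-injection record of the solicited symptoms, so complaints already present on Day 0 cannot be reliably separated from vaccine reactogenicity

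*Protocol*

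**What the plan says.** The primary endpoints in section 4.3 include "Frequency and severity of systemic reactogenicity signs and symptoms until day 14 post vaccination (solicited general symptoms"). No condition is attached that a symptom be new, or worse than before injection. Section 6.5 (Specification of Safety Endpoints) describes the window as "The nature, frequency, and severity of solicited AEs occurring from the time of injection through 14 days following the procedure", and its recording subsection repeats it: "Solicited AEs will be collected from the time of administration of investigational product through 14 days following the procedure".

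Section 6.4 fixes when the list is asked about: "Review solicited symptoms (4 visits; Visits 3, 4, 5, 6". In Table 3 those visits are Days 1, 2, 7 and 14.

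On Day 0, section 6.3 lists before the injection "Review of subject's medical history (including concomitant medications) since previous visit", a check of the entry criteria, "Directed physical examination (proposed injection site) and vital signs check" and a pregnancy test for women. After the injection it lists a repeat site examination, repeat vital signs and "Review of any immediate AE". Table 3 also marks AE monitoring at Visit 2.

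Among the exclusions in section 5.4 is "Moderate or severe illness and/or fever" above 38°C in the preceding week. Named conditions such as migraine also exclude, but a mild non-specific complaint does not.

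All seven cohorts receive vaccine (synopsis, Sample Size). Section 4.1 states that 60 adults had been vaccinated by Amendment 3: 20 in cohort 1, 39 in cohort 2 and one in cohort 3.

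**The concern.** Most of the solicited list in section 6.5 is subjective and common in everyday life: chills, muscle ache, joint ache, fatigue, headache, stomach upset. After injection each item is prompted by name. Before injection there is only an open history. Someone with a mild headache on the morning of Day 0 may not mention it unprompted, and may then report it when asked on Day 1. Nothing on record would show that it came first.

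A control arm would reveal the background rate, but this trial has none. What is at stake is the absolute frequency of reactogenicity at each dose, which is a primary result and is to be compared with other sites in the consortium. Joint symptoms deserve particular care, because section 4.6 notes arthritis cases with the same batch in Switzerland. The gap lies in data collection: an analysis plan can define how a pre-existing symptom is handled, but it cannot recover a value that was never recorded.

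**Working it through.** **Stated figures.** Cohort sizes in the synopsis: 20 + 20 + 20 + 39 + 62 + 20 + 20 = 201, as stated. Vaccinated by Amendment 3: 20 + 39 + 1 = 60. Still to come: 201 − 60 = 141, which is 61 in cohort 3 and 20 in each of cohorts 4 to 7 (61 + 80 = 141).

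**What has a same-day baseline.** Fever: yes, from vital signs. Local signs: yes, from the site examination. Headache, fatigue, myalgia, arthralgia, chills, gastrointestinal symptoms: only if raised in the general history, and without a required grade.

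**Possible size.** The protocol gives neither a Day 0 symptom prevalence nor an expected reactogenicity rate, so both are assumed here. Let p be the true vaccine-caused rate and b the Day 0 prevalence, taken as independent of each other. If every existing symptom were counted (an upper bound), then

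observed = p + (1−p)×b, so the excess is (1−p)×b.

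| b | p = 10% reads | p = 30% reads | p = 50% reads |
|---|---|---|---|
| 2% | 11.8% | 31.4% | 51.0% |
| 5% | 14.5% | 33.5% | 52.5% |
| 10% | 19.0% | 37.0% | 55.0% |
| 20% | 28.0% | 44.0% | 60.0% |

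Expected number already symptomatic, n×b for b = 2% to 20%: 0.4 to 4.0 in a group of 20, 1.2 to 12.4 in the group of 62, and 4.0 to 40.2 among all 201.

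**Effect on a dose contrast.** With the same b in both groups, the difference shrinks by the factor (1−b).
- True 20% v 60%, n = 20 v 62: the 40-point difference reads 39.2 points (b = 2%) to 32.0 points (b = 20%). Approximate power (two-sided 5%, normal approximation for two proportions) falls from 91% to between 90% and 73%.
- True 20% v 40%: at b = 5%, 24% v 43%, ratio 1.79; at b = 20%, 36% v 52%, ratio 1.44. The true ratio is 2.0.
- Equal true rates stay equal, so no false difference arises.

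**Testing the obvious remedy.** Suppose the primary summary counted only new or worsened symptoms. Cohorts 1 and 2 have no pre-dose record and would stay unadjusted, while cohort 3 (all but one person) would be adjusted. Assume a vaccine-caused symptom in someone already symptomatic shows as a worsening. Then, with true 20% in cohort 1 and 40% in cohort 3:
- b = 5%: 24% v 40%, ratio 40/24 = 1.67
- b = 20%: 36% v 40%, ratio 40/36 = 1.11

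Both lie further from 2.0 than the unadjusted 1.79 and 1.44. With an equal true 30% and b = 20%, cohort 2 would read 44% and cohort 3 would read 30%, a difference created by ascertainment alone.

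**The case against.** A reader might infer that existing mild symptoms are counted as vaccine reactions. The protocol does not say so, and several passages point the other way. The annex defines an AE as arising during or after administration. The solicited window opens at injection. Section 6.5 asks for a relationship to the product for each AE, considering timing, concurrent illness and other causes. This stands as far as it goes, and it limits the claim to symptoms that may be counted. It does not close the gap: applying the definition needs the pre-dose state, and the causality filter is uneven, since section 6.5 asks for it for all AEs while the annex mentions only unsolicited ones.

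A reader might also infer that nothing is asked before injection, or that the pre-dose state is the only internal reference. Neither is right. Day 0 includes history, medications, site examination and vital signs, and immediate reactions are reviewed after the injection the same day. The memory aid, diary card and CRF are not shown. The lower-dose groups are also an internal reference, and randomised groups should have similar Day 0 symptoms. That protection is only partial: cohorts 1 and 2 were filled before the new randomisation list for cohorts 3 to 5, and cohorts 6 and 7 are not randomised.

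Finally, the prevalence is assumed. In healthy volunteers it could be low, and at 2% the effect on power is about one point. That stands.

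**Conclusion.** The point holds in limited form. The protocol plans no itemised, graded record of the subjective solicited symptoms before injection, admits people with mild symptoms and has no unvaccinated group. Existing complaints therefore cannot be reliably separated from reactogenicity and may enter the primary endpoint.

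The consequence is mainly for absolute rates. The excess is at most (1−p)×b: 1.8 to 18 percentage points at a true 10%, and 1.0 to 10 points at a true 50%, for b from 2% to 20%. These figures rest on an assumed prevalence, on independence of Day 0 symptoms from the vaccine effect, and on every existing symptom being counted; the real effect may be much smaller. Contrasts between concurrently randomised doses are diluted rather than biased towards a difference. This is a cheap improvement in how the primary rates can be read, not an error that invalidates them.

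**What to change.** In section 6.3 and Table 3, add one step at Visit 2 before the injection: record each item of the section 6.5 solicited list with its severity, for the 141 participants still to be vaccinated.

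Keep the all-cohort primary reactogenicity summary on the same unadjusted basis for everyone. Add a supplementary summary that counts only symptoms that are new or more severe than before injection, restricted to participants with a pre-dose record: 61 of cohort 3 and all of cohorts 4 to 7. State that these adjusted rates are not to be compared with the unadjusted rates of cohorts 1 and 2.

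Cost: a few minutes and one CRF page at a visit that already takes place. The first 60 vaccinees will have no adjusted figure, and that cannot be repaired.
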